##### Order sets review

To evaluate Behavior and Results domains of our evaluation model, an assessment will be conducted through 10-min structured interviews approximately 6-, 12-, and 18-months post-workshop training. An interview guide is provided in Supplementary File 2. Based on our experience from our Operatic 1.0 trial, this time interval is sufficient for ASPs to implement order set modifications across different surgical specialties, and participants are generally able to recall the work they have accomplished. The interview will inquire whether an order set modification was made, or a new order set developed (Yes/No, and number). For each impacted order set, we will inquire about the targeted procedure, the previous duration (no post-op antibiotics, 24 h or less, 25–48 h, or 48 h or more), and any changes in duration (eliminated, shortened, or no change). If the post-operative duration has been shortened, we will specify to what extent: no post-op antibiotics, 24 h or less, or 25–48 h. We anticipate some loss to follow-up due to staff turnover. In such cases, we will attempt to identify an alternative respondent, describe the study, and determine whether guideline integration through order set changes has continued.

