#### Distal implementation outcomes (order set changes)

We will also analyze distal implementation outcome measures descriptively, using these results to inform analyses of clinical outcomes. In our Operatic 1.0 study, we encouraged participants to target surgical procedures that they felt were modifiable, and, as a result, different ASPs targeted different procedures in their respective hospitals. We will descriptively analyze these results to understand which procedures are successfully targeted for order set changes and which facilitation skills are being used over time. This information will guide our clinical analyses to understand what surgical specialties and/or specific procedures are likely to have been most impacted (e.g., spine procedures). As appropriate, we will fit general linear models to evaluate change in our implementation outcomes before and after the workshop long term.

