### Clinical outcomes

#### Primary hypothesis

We hypothesize that the appropriately lagged post-intervention percentage of cases receiving unnecessary postoperative antibiotic prophylaxis will be significantly lower than in the pre-intervention period. To test this hypothesis, we will use an intention-to-treat approach for the primary analysis, including all complete case patient data from the NSQIP-P analysis set. A mixed-effects logistic interrupted time series (ITS) regression model will assess the impact of "order set change resulting in reduction" (1) versus "no order set change" (0) on prophylaxis prescriptions. The model will include the intervention (pre vs. post), time (in months), and an interaction term between time and intervention, including a random intercept to account for intra-hospital correlation in the model. The post-intervention slope (β_2) will be the primary estimate of interest (Fig. 2), but we will also investigate differences at 12, 24 and 36 months. The interruption point will be 12 months after each hospital’s first training, with sensitivity analyses at lags 9, 15, and 18 months as well. We will extend the model to adjust for age, surgical subspecialty, procedure type, hospitalization duration, and co-morbidities using Akaike information criterion (AIC)-based variable selection. Subgroup analyses by procedure type and hospital will also be conducted.

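### The order-set interview codes overlap at 48 h, have no extent code above 48 h and allow complete removal to be entered two ways, which blurs the recorded size of change

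*Protocol article*

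**What the plan says.** Order sets review (Data collection, Implementation data) describes 10-minute structured interviews about 6, 12 and 18 months after training. The duration items apply to affected order sets: "For each impacted order set, we will inquire about the targeted procedure". Three items then follow.

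- Baseline: "the previous duration (no post-op antibiotics, 24 h or less, 25–48 h, or 48 h or more".
- Change, asked directly: "any changes in duration (eliminated, shortened, or no change".
- Extent, asked only after one of the change answers: "If the post-operative duration has been shortened, we will specify to what extent: no post-op antibiotics, 24 h or less, or 25–48 h".

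Two later sections use order-set results. Distal implementation outcomes (order set changes) states: "We will also analyze distal implementation outcome measures descriptively, using these results to inform analyses of clinical outcomes". It adds that the results will show which specialties or procedures were probably most affected. Under Clinical outcomes, Primary hypothesis, the model contrasts "order set change resulting in reduction" (coded 1) with no order set change (coded 0).

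**The concern.** A coding scale should give each order set exactly one place, and the before and after scales should match so that they can be cross-tabulated. The printed items fail on three counts. The top two baseline categories share the value 48 h. The baseline scale has an upper category that the extent scale lacks. One end state, no postoperative antibiotics, can be reached by two answer paths.

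What is at stake is the description of how far durations moved. That description helps decide which procedures the clinical analyses concentrate on. The answers also rest on recall, and the article expects substitute respondents after staff turnover. Codes that are not mutually exclusive let two respondents place the same order set differently at different interviews.

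**Working it through.** This is a question of category logic. The article gives no figure to reproduce, and no power or error-rate calculation applies. The check passes durations in whole hours, from 0 to 120 h, through the three items as printed.

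**Scales used**

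- Previous duration: none (0 h); 24 h or less; 25–48 h; 48 h or more.
- Change: eliminated; shortened; no change.
- Extent, only if shortened: none; 24 h or less; 25–48 h.

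**Coverage**

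- Whole hours with more than one previous-duration code: 48 h only.
- Whole hours with no extent code: every value from 49 h upward.

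**Example order sets**

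| Before → after (h) | Previous-duration code | Change | Extent code |
|---|---|---|---|
| 48 → 48 | 25–48 or 48+ | no change | not asked |
| 72 → 72 | 48+ | no change | not asked |
| 96 → 72 | 48+ | shortened | none fits |
| 72 → 49 | 48+ | shortened | none fits |
| 72 → 48 | 48+ | shortened | 25–48 |
| 48 → 36 | 25–48 or 48+ | shortened | 25–48 |
| 48 → 24 | 25–48 or 48+ | shortened | 24 or less |
| 48 → 0 | 25–48 or 48+ | eliminated (or shortened) | not asked (or none) |

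**What follows from the table**

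1. *Overlap.* The 48 → 36 h set moves no category if its baseline is coded 25–48 h, and one category if coded 48 h or more. The 48 → 24 h set moves one category or two. The facts are the same in each case, and the recorded size of change depends only on which baseline code was chosen.
2. *Missing extent.* For 96 → 72 h and 72 → 49 h the shortening is captured but its extent is not.
3. *Two routes to removal.* The last row can be answered in two ways. If n order sets lost postoperative antibiotics altogether and k of them were entered as shortened to none, a count of eliminated alone gives n − k. No rule for pooling the two is stated.
4. *The reduction indicator.* Every real cut in the table is recorded as shortened or eliminated, and each unchanged set is recorded as no change. On the printed items, none of the three faults moves a set across the 1/0 boundary.

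**Check on the remedy.** Suppose change were derived only from repaired categories (none; more than 0 to 24 h; more than 24 to 48 h; more than 48 h). Then 96 → 72 h lies in the top category both times, and 48 → 36 h lies in the third category both times. Both real cuts would appear unchanged. The direct change question therefore has to stay, with the hours recorded beside it.

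**The case against.** A reader might infer two stronger conclusions, and the documents support neither.

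- *That an unchanged 48 h set can be scored as a reduction.* Change is asked directly with a no-change option, and extent is asked only after shortened, so no resulting category is collected for an unchanged set. A false reduction would need an inconsistent answer, or an analyst who ignored the change item and compared categories. The article describes neither.
- *That a real cut remaining above 48 h is lost to the primary clinical model.* It is recorded as shortened, and that is enough for a 1. Only its extent has no code.

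The other side has further points. The Abstract names guideline-congruent order sets as the primary implementation outcome, not these duration codes. If congruence is read against the guideline summarised in Background, which for the cases it covers ends prophylaxis at incision closure, a 48 h set has the same status under either baseline code, and a set cut to 72 h does not become congruent. The two routes to removal record one end state and can be merged at analysis without loss. Order-set results are analysed mainly descriptively. Recall and staff turnover are limitations that the article already acknowledges, and the category wording does not cause them. An interviewer can clarify a boundary answer. The interview guide itself, Supplementary File 2, is not shown and may word the options differently.

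Most of this stands, and it limits the point to the size-of-change description. It does not remove the point. The overlap and the missing extent option are in the article's own text. Merging the two removal answers works only if the analyst knows to do it. If the guide is worded correctly, the article misdescribes it and the two still need aligning.

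**Conclusion.** The point holds as a low-severity coding fault. The items as printed give an ambiguous baseline category for sets that stop at exactly 48 h and no extent for shortened sets that remain above 48 h. A count of eliminated sets can also be too low if the second route to removal is not pooled with it. The effect falls on the descriptive size-of-change results and on any choice of procedures or specialties for clinical analysis that relies on them.

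No effect on the primary clinical model's reduction indicator is shown. How common the affected order sets are cannot be judged, because the documents do not give the distribution of stop times.

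The conclusion assumes that interviews follow the items as the article prints them and that change is taken from the direct question.

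**What to change.** - Use one scale for both previous and resulting duration: none; more than 0 to 24 h; more than 24 to 48 h; more than 48 h.
- Record the stop time in hours for both, so that a cut within one category is still measured.
- Keep the direct change question and check each answer against the recorded hours. Do not replace it with a comparison of categories.
- State that shortened to none is counted as eliminated.
- Make the text of Order sets review and the interview guide (Supplementary File 2) agree.

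The cost is one or two extra fields per order set in an interview that already takes place, with no extra contact if the change is made before the first 6-month interview. Made later, extents above 48 h that had not been collected would have to be recovered by going back to respondents.

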#### Missing data

Based on our previous studies, since we do not foresee a large percentage of either endpoint or covariate missingness in the data, the primary analysis will consider the complete case data only. If the level of missingness exceeds 5% for any specific covariate of interest, then multiple imputation under the missing at random (MAR) assumption will be performed [33]. The estimates from the fitted models with these full data sets will be compared with those from the complete case analysis, and any discrepancies will be discussed in subsequent scientific publications. Furthermore, following these analyses if the MAR assumption is deemed questionable, then appropriate sensitivity analyses will be performed to investigate plausible departures from this assumption [34].

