A key strength of this study is its multi-center design, which enhances the generalizability of findings across diverse hospital settings. The inclusion of at least 20 hospitals participating in both the SHARPS Collaborative and NSQIP-P ensures that the intervention is tested in varied environments with different levels of ASP maturity and institutional support. Additionally, the use of a time-series analysis allows for the evaluation of long-term trends and the sustainability of the intervention’s effects. However, this study has potential limitations. The quasi-experimental design and interrupted time series analysis, while robust, do not entirely eliminate the possibility of confounding variables that may not have been captured or controlled for in our hospital demographics and individual participant characteristics, potentially influencing the observed outcomes. Additionally, reliance on NSQIP-P data for clinical outcomes may introduce delays in data availability. Another challenge is participant attrition, particularly in follow-up interviews assessing long-term implementation outcomes. While targeted recruitment and incentives will be used to mitigate this issue, some loss to follow-up is expected. Lastly, because this study is mostly conducted in tertiary-care children's hospitals, its findings may not be generalizable to other clinical settings, such as community hospitals.

The results of this study will inform future efforts to refine and optimize ASP facilitation strategies. If successful, the training model could be expanded to other pediatric and adult surgical settings, with potential adaptations based on specialty-specific prescribing patterns. This study represents a significant step toward improving antibiotic stewardship in pediatric surgery by addressing both the technical and relational aspects of implementation. The findings will provide critical evidence for disseminating and implementing facilitation and order set modifications to de-implement unnecessary post-operative antibiotics at children's hospitals in the United States.

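### The primary model names two exposures; one rests on interviews where loss is expected, so a complete-case primary analysis could drop hospitals whose NSQIP-P outcomes exist

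*Protocol article*

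**What the plan says.** **Exposure (Protocol article, Primary hypothesis).** "A mixed-effects logistic interrupted time series (ITS) regression model will assess the impact of" a 1/0 variable, where 1 is "order set change resulting in reduction" and 0 is no change to the order set. No code is given for unknown. The next sentence lists different terms: "The model will include the intervention (pre vs. post), time (in months), and an interaction term between time and intervention", with a random intercept for hospital. The break is timed from training: "The interruption point will be 12 months after each" hospital is first trained. The analysis is labelled intention-to-treat and is said to use complete-case patient data from NSQIP-P.

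**Source of order-set status (Order sets review).** Structured interviews at about 6, 12 and 18 months after the workshop. "We anticipate some loss to follow-up due to staff turnover"; the team will then try to find another respondent. The Discussion repeats the expectation: "Another challenge is participant attrition, particularly in follow-up interviews assessing long-term implementation outcomes".

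**Missing data.** Little endpoint or covariate missingness is foreseen, so "the primary analysis will consider the complete case data only". Multiple imputation under MAR follows if a covariate of interest is more than 5% missing, and is compared with the complete-case result. Sensitivity analyses follow if MAR is doubted.

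**Power and sample size calculations.** No missing data are assumed.

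**The concern.** The outcome and the order-set status reach the analysis by different routes. Postoperative antibiotic duration is recorded by the NSQIP-P abstractor (Clinical data), whoever still works on the stewardship team. Order-set status depends on someone at the hospital being interviewed.

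The status belongs to a hospital, or to a procedure within a hospital. If it is the fitted exposure and is unknown, a complete-case rule removes all the affected cases at once. The primary analysis would then exclude trained hospitals because of something that happened after training, which the intention-to-treat label rules out. The exclusion may also be informative, since staff turnover may be related to how far the order-set work got.

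The justification for complete-case analysis speaks of endpoint and covariate missingness. It does not take account of the loss that two other sections expect in the variable named as exposure.

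**Working it through.** **1. The two readings**

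| | Order-set code fitted | Only the listed terms fitted |
|---|---|---|
| Exposure | change with reduction (1) vs no change (0) | pre vs post, break at training + 12 months |
| Source | interviews | training date |
| Can be missing? | yes; loss is expected | no |
| Complete-case effect | uncoded hospital or procedure leaves | no case leaves |
| Consistent with intention-to-treat? | no, if hospitals leave | yes |

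The same section supports both columns, and nothing in the article chooses between them.

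**2. Does the imputation clause close the gap?** Take exactly 20 hospitals of equal size (an assumption; the article says at least 20). One hospital is 1/20 = 5%, which does not exceed the trigger; two are 2/20 = 10%, which does. Once triggered, imputation and any departure-from-MAR analysis are compared with the complete-case result and do not replace it. It is also unstated whether the order-set code counts as a covariate for this clause.

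**3. Direction of bias.** Suppose order sets change in a share π of hospitals, with effect d in those and 0 elsewhere, and that changers and non-changers are retained with probabilities r1 and r0.
- Average pre/post effect among retained hospitals: d·π·r1 / (π·r1 + (1−π)·r0). This exceeds dπ in size when r1 > r0. But the average pre/post effect is the target only under the right-hand column, where no hospital leaves, so r1 = r0 = 1 and it equals dπ.
- Changer versus non-changer contrast (left-hand column): d − 0 = d for any r1 and r0. It is biased only if loss depends on prescribing beyond what the code captures.

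**4. Precision.** The plan's figure is at least 80% power for a difference of at least 5% from 45%, with 20 hospitals, 10 steps, 14 cases per hospital-month, ICC 0.12 and two-sided 5%. I used the Hussey-Hughes variance:

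v = I·s²(s² + T·τ²) / [(I·U − W)s² + (U² + I·T·U − T·W − I·V)τ²], power = Φ(|p0 − p1|/√v − 1.96).

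Here I is the number of hospitals and T the number of periods. U is the total number of exposed hospital-periods; W and V are the sums of squared exposed counts by period and by hospital.

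For 45% vs 40%, the mean binomial variance is (0.2475 + 0.2400)/2 = 0.24375. So τ² = 0.12 × 0.24375 = 0.02925 and s² = 0.88 × 0.24375/14 = 0.01532. With 11 monthly periods, U = 110, W = 1540 and V = 770, giving v = 0.00082 and power Φ(0.05/0.02864 − 1.96) = 0.415.

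Other layouts, and the mean power after removing hospitals at random (numbers lost are assumptions):

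| Layout | 0 lost | 1 | 2 | 4 | 6 |
|---|---|---|---|---|---|
| 11 monthly periods | 0.415 | 0.397 | 0.379 | 0.341 | 0.303 |
| Monthly, 12 pre and 36 post | 0.602 | 0.579 | 0.554 | 0.502 | 0.450 |
| 11 equal periods over 60 months (about 76 cases each) | 0.980 | 0.974 | 0.967 | 0.946 | 0.913 |

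Reading 5% as relative (45% to 42.75%) gives 0.12 to 0.17. A before/after model without period effects gives above 0.99, and still 0.995 with six hospitals lost. The stated 80% is not uniquely reproducible, because the period layout and the meaning of 5% are not fixed. Losing six hospitals costs from under 1 point to about 15, depending on layout.

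**The case against.** The strongest reply is that case loss is inferred. The terms actually listed need no interview, and the complete-case phrase refers to patient data in NSQIP-P, which can be read as excluding interview data. This stands: case loss is conditional on the order-set code being fitted. It does not settle the matter, because the preceding sentence says the model assesses that code. If complete-case covers NSQIP-P variables only, an unknown code then has no rule at all.

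Second, the plan does more about loss than one sentence suggests. It schedules three interviews, seeks an alternative respondent, and mentions targeted recruitment and incentives in the Discussion. An order set is an institutional fact that a successor can report. All this stands, and it reduces how many hospitals would end up uncoded. It does not say what happens to those that do.

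Third, a condensed article may leave the coding of a missed interview to the full plan. That also stands, and the absent code alone would be no finding. The point rests on what the article does fix: two exposures for one model, and a low-missingness premise beside an expectation of loss.

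A reader might go further and infer that the training effect will be overstated, because hospitals that lost their champion are the non-changers. The documents do not support that. As step 3 shows, this shift appears under neither stated reading. It would need a third that the article does not describe: a pre/post model fitted only to hospitals with a known code.

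**Conclusion.** The point holds in conditional form. The Primary hypothesis section names two exposures. Under one, the complete-case rule can remove whole hospitals or procedures with recorded outcomes, against the stated intention-to-treat approach and possibly selectively. Under the other, nothing is lost.

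No size can be attached. The article gives no interview-loss rate, no share of hospitals expected to change order sets, and no link between turnover and prescribing. The power figures above rest on assumed losses and an unfixed period layout, so they show sensitivity only. Nor can a reader conclude that hospitals will be lost, or that the analysis is complete-case throughout: imputation and departure-from-MAR analyses are provided, as conditional comparisons. The ambiguity should be resolved before analysis, because it decides which hospitals the primary result describes.

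**What to change.** - **Primary hypothesis:** define the primary exposure solely as pre/post by each hospital's training date plus the stated lag. State that every hospital with NSQIP-P data stays in the primary analysis whether or not interviews were obtained.
- **Primary hypothesis:** move the order-set change (1/0) contrast to a secondary analysis.
- **Missing data:** state that interview status does not enter the primary complete-case rule.
- **Secondary contrast:** carry forward the last known order-set status. Where status was never obtained, report the result with it scored as unchanged and again as changed. Neither score is right in itself; the pair shows how far the unknown status matters.

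The cost is a few sentences and one extra sensitivity run, with no new data. The downside is that the training-date effect may be diluted by hospitals that made no order-set change; the secondary contrast is where that is examined.

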#### Clinical data

Clinical data will be gathered using the NSQIP-P database to assess overall impact on appropriate post-operative antibiotics prescribing and usage. De-identified, case-level clinical outcome data from NSQIP-P will be requested from each hospital shortly after participation in the workshop and subsequently on an annual basis until we have obtained three years of data post workshop participation. Each participating hospital adheres to the protocols and definitions outlined in the NSQIP-P Manual of Operations. Data abstraction at each site is performed by a full-time NSQIP-P data abstractor, typically a pediatric nurse with clinical expertise, who undergoes thorough training to ensure precise and reliable data collection. Data are gathered for 35 cases every 8 days at each hospital, contributing to a dataset of up to 1,500 cases annually. Since December 2018, antibiotic prophylaxis data for each case includes the type of antibiotic used, the timing of administration (within 1 h before incision), whether redosing occurred, and the duration of postoperative antibiotic use. Data collection continues for 30 days post-surgery to monitor for potential complications, such as SSI and CDI, which may appear up to a month after the procedure. Data elements include basic demographics (age, sex, date of procedure), type of procedure, wound class (clean, clean-contaminated, contaminated, or dirty), comorbidities, and resources utilized during surgery.

